### **Sample size and justification**

Three hundred participants provides 90% power, at the 5% significance level (two-tailed) to detect a difference of around 3 points between the groups in mean EASI scores over 2, 4 and 6 months using a repeated measures analysis of covariance, assuming a SD of 13, a correlation between EASI scores at different time points of 0.6 and loss to follow up of 10%.

A 3-point improvement in EASI represents a small but still clinically meaningful difference between groups, and we are keen to ensure that the study is sufficiently powered to detect this magnitude of difference since it is unlikely that a trial like this will be done again. A small treatment response could still be worthwhile to the NHS since this non-pharmacological treatment is assumed to have no adverse effects, and because eczema affects so many people. It is also likely that a relatively small response on the objective primary outcome will be reflected in larger, more clinically meaningful treatment effects in the patient-reported outcomes.

Participants will be recruited from six recruiting centres over an 18 month recruitment period. Recruitment is expected to increase gradually over the first 6 months of the trial to allow for staggered site set-up.

### **Procedures for missing, unused and spurious data**

Every effort will be made within the trial to minimise the occurrence of missing data. All missing data items will be tabulated by treatment arm and reasons given where possible. We will examine the plausibility that data are missing at random (MAR) and multiple imputation techniques will be used to handle missing values as appropriate.

Data from the parent / guardian and child focus groups and interviews and prescriber and commissioner interviews will be analysed separately using a manual process of thematic analysis. Audio tapes will be transcribed verbatim. Transcripts, notes and artefacts (as explained by children) will be reviewed in detail, coding the substance of the data. Theoretical codes will be added beside each code as a reminder of any thoughts or questions attached to the codes. As codes develop they will be compared with the aim of identifying similarities and differences amongst incidence in the data. The identified codes will be condensed into higher levels of abstraction to form categories; these will be continuously reviewed to ensure that they cover variations within the data. The final step will be to interpret the categories so that better understanding is achieved. To ensure trustworthiness members of the research team will be involved in the analysis process.

Data from this qualitative study will be linked with data from the RCT to provide a rounded assessment of the impact of wearing silk garments and the patient-reported factors that may influence this.

## COST-EFFECTIVENESS ANALYSIS

### Objective:

To estimate the within trial cost-effectiveness of silk therapeutic clothing with standard care compared to standard care alone from an NHS and a family perspective.

The cost analysis will compare the overall costs for the intervention to standard care, measuring resource use such as primary care contacts, medication prescribed, secondary care contacts and patient costs. Health and family resource use data will be recorded by research nurses. The patients will be asked to collect data on a diary which will serve as an aid memoire.. Resource use will be valued using published unit costs (e.g. Curtis and Netten ([PSSRU 2004](#)), BNF 2005, and NHS reference costs and patient reported estimates. The costs to the NHS and patient will be reported separately as well as in combination.

The primary measures of effectiveness for the cost effectiveness analysis will be the difference in number of participants who achieved “treatment success” (defined as those with at least a 50% improvement in EASI at 6 months compared to baseline). Secondary analyses will be conducted using continuous data from the EASI scale; the Dermatitis Family Impact Scale; eczema specific utility measures (Stevens 2005) and generic measures of health utility as measured using the EQ-5D-3L (for the main carer) and the Children's Health Utility Index 9D (CHU-9D) for children. A cost utility analysis where effectiveness is measured in terms of the Quality Adjusted Life Years (QALYs) for child and main carer will be undertaken (using linear interpolation and area under the curve with baseline adjustment).

If non-dominance occurs an incremental cost-effectiveness ratio will be produced. Sensitivity analysis will be undertaken to test the robustness of results in the face of any uncertainties or assumptions made in the analysis.

### ADVERSE EVENTS

It is unlikely that silk clothing will result in any adverse effects. As such AEs will not be collected for this trial, but ALL SAEs will be.

A worsening of eczema and infected eczema will not be considered as adverse events as these data will be collected as specific endpoints for the trial. A worsening of eczema will be detected using the scores from EASI.

Hospitalisation due to eczema will be captured as a Serious Adverse Event (SAE).

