## **DURATION OF THE TRIAL / STUDY AND PARTICIPANT INVOLVEMENT**

The overall duration of the study is anticipated to be approximately 36 months. It is planned that recruitment will take up to 18 months. Target recruitment for the pilot phase of the trial is 75 participants enrolled over the first 6 months of recruitment.

Each participant will participate in the trial for 8 months (treatment period) and her/his participation will commence upon signing the consent form. Participants will be randomised to intervention or control groups for the first 6 months. Participation in the RCT will end after 6 months, at which point participants in the control group (standard care) will be given the therapeutic clothing and will be followed up until 8 months post randomisation. Participants allocated to the intervention group will continue with their randomised intervention until the garments are no longer usable. Further supplies of clothing will not be given to these patients during the follow-up period from 6 to 8 months post-randomisation.

Participation in the qualitative component will be a maximum of 2.5 additional hours after completing their final 8 month contact.

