| Use of wet and dry wraps                                                                          | √                 | √         | √         | √         |          |
| On-line questionnaire (weekly) including POEM, topical treatment use and use of wet and dry wraps |                   | √         | √         | √         |          |
| Final on-line questionnaire                                                                       |                   |           |           |           | √        |
| DFI                                                                                               | √                 |           |           | √         |          |
| EQ-5D-3L of parent                                                                                | √                 |           |           | √         |          |
| Child utility scales (ADQoL, CHU-9D)                                                              | √                 |           |           | √         |          |
| Number of infections                                                                              | √                 | √         | √         | √         |          |
| Serious adverse events                                                                            |                   | √         | √         | √         |          |
| NHS and family resource use                                                                       | √                 | √ & Diary | √ & Diary | √ & Diary | √        |
| Adherence                                                                                         |                   | Ques      | Ques      | Ques      | Ques     |
| Durability of clothing                                                                            |                   |           |           | √         | √        |
| Acceptability (parent & child)                                                                    |                   |           |           | √         | √        |
| Replace garments if required (intervention group only)                                            |                   | √         | √         |           |          |

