### **End of Trial Follow-up Questionnaire**

Parents / legal guardians of participants will be sent an end of trial follow-up questionnaire (on-line or postal) at eight months post-randomisation. This will seek information about current eczema status, adherence, acceptability and their opinion of the therapeutic clothing.

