### **Criteria for terminating trial**

This trial involves CE marked clothing that are being used within their normal licensing authorisation. As such, it is very low risk. However, if severe adverse effects associated with the clothing occur frequently, the study may be terminated on the advice of the Trial Steering Committee.

The Investigator may stop the trial or terminate one centre if new information becomes available causing major safety concerns, or if there are issues with trial conduct.

Should the trial be terminated the research data will not be destroyed.

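### The protocol promises all serious adverse events over an 8-month participation, but Table 2 schedules SAE and skin-infection collection only to 6 months, when controls first receive the garments

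*Protocol*

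**What the plan says.** **The promise.** The Adverse Events section says: "As such AEs will not be collected for this trial, but ALL SAEs will be". No start or end of the collection period is given there. Under Safety endpoints, the one named endpoint is patient-reported skin infection needing antibiotic or antiviral treatment; beyond that, only serious events are collected.

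**The period.** The section on duration and participant involvement sets participation at 8 months and calls this the treatment period. At 6 months, "participants in the control group (standard care) will be given the therapeutic clothing and will be followed up until 8 months post randomisation". For the other arm, "Participants allocated to the intervention group will continue with their randomised intervention until the garments are no longer usable". Both arms may therefore be wearing silk between months 6 and 8.

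**The schedule.** In Table 2 the row "Serious adverse events" is ticked at 2, 4 and 6 months. The row "Number of infections" is ticked at 0, 2, 4 and 6 months. Both are blank at 8 months.

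**The 8-month contact.** The section on the end-of-trial questionnaire describes it thus: "This will seek information about current eczema status, adherence, acceptability and their opinion of the therapeutic clothing".

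**The termination criterion.** Under Criteria for terminating trial: "if severe adverse effects associated with the clothing occur frequently, the study may be terminated on the advice of the Trial Steering Committee".

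**The concern.** An unqualified promise to collect all SAEs, read with an 8-month participation, implies SAE collection for 8 months. The schedule of assessments stops at 6. The boundary falls at the worst point for safety information: the visit at which scheduled collection ends is also the point at which control children are supplied with the device.

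At stake is the completeness of the safety record for the garments in the open period, in children. If the trial later reports SAEs and treated infections among garment wearers, the count for months 6 to 8 will depend on events that happened to come to a site's notice. A low count could not be told apart from low ascertainment.

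A smaller, related mismatch concerns the termination criterion. It turns on *severe* effects of the clothing, whereas the trial collects *serious* events and treated infections. These are different classes, and the criterion also gives no meaning for *frequently*.

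**Working it through.** The protocol states no figure on this point, so there is none to reproduce. The check is a cross-reading, followed by simple arithmetic to size the gap.

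**1. Is there any scheduled route for SAEs or infections after month 6?**

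| Possible route | What the protocol provides | Covers months 6 to 8? |
|---|---|---|
| Table 2, SAE row | 2, 4, 6 months | No |
| Table 2, infections row | 0, 2, 4, 6 months | No |
| Nurse visits (Data Collection Methods) | Baseline, 2, 4, 6 months | No |
| Weekly questionnaire | Table 2 ticks 2, 4, 6 months; the Compliance section ends weekly adherence reporting at 6 months; no SAE item is listed | No |
| 8-month questionnaire | Eczema status, adherence, acceptability, opinion | No SAE or infection item listed |
| NHS and family resource use, Table 2 | Ticked at 8 months | Indirectly: an admission might show |
| Site reporting (Trial Intervention-related SAEs) | All SAEs, no end date | Passively: only if the site hears of it |

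No scheduled contact is stated to ask about SAEs or infections after 6 months.

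**2. Do the substitutes named under Adverse Events survive month 6?** That section leaves worsening and infected eczema out of adverse events because they are collected as trial endpoints, with worsening detected by EASI. EASI and infections both end at 6 months in Table 2. Parent-reported eczema status at 8 months is the only remnant. The section also says that admission for eczema will be recorded as an SAE, but no scheduled step does this after month 6.

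**3. Size of the window.** Inputs: N = 300 (Trial Configuration); intervention children exposed for months 0 to 8; controls exposed for months 6 to 8. Assumptions: no dropout and continuous wear. The allocation ratio is not stated, so it is varied.

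Exposed child-months = 8 × n(silk) + 2 × n(control). Child-months after month 6 = 2 × [n(silk) + n(control)] = 600 in every case.

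| Silk : control | Exposed child-months | After month 6 | Share | Controls' part of total | First exposures at month 6 |
|---|---|---|---|---|---|
| 150 : 150 | 1,200 + 300 = 1,500 | 600 | 40% | 300 (20%) | 150 of 300 (50%) |
| 200 : 100 | 1,600 + 200 = 1,800 | 600 | 33% | 200 (11%) | 100 of 300 (33%) |
| 100 : 200 | 800 + 400 = 1,200 | 600 | 50% | 400 (33%) | 200 of 300 (67%) |

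**4. How far do the assumptions inflate this?** Two checks at 1:1:

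- Apply the protocol's 10% loss wholly at month 6. Late exposure is 0.9 × 600 = 540, the total is 900 + 540 = 1,440, and the share is 37.5%.
- Suppose instead that every intervention garment is unusable from month 6, since none is replaced. Late exposure is 300, the total is 900 + 300 = 1,200, and the share is 25%.

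The 40% is therefore an upper figure for 1:1. In every case all control-arm first exposures lie in the window.

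**5. Termination criterion.** Up to month 6 it can draw on SAEs and treated infections. An effect that is severe, but neither serious nor a treated infection, has no planned collection route.

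**The case against.** **This is silence rather than contradiction.** The Adverse Events section gives no window. Sites must report all SAEs with no end date. Table 2 separates the RCT from an observational period, and the duration section says that participation in the RCT ends at 6 months. Part of this stands: reporting does not formally stop, only scheduled ascertainment does. Yet the same section keeps children in the trial to 8 months, and End of the Trial ends the RCT only when the last questionnaire arrives. An open-ended duty on sites that have no scheduled contact with the child is weak support for a promise to collect every SAE.

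**The 8-month questionnaire may ask more than its summary lists.** This is fair. The summary omits garment durability and GPs' willingness to prescribe, both of which other sections place at 8 months. Resource use is also recorded then and could reveal an admission. But nothing says that such an entry triggers an SAE report, and Table 2, which does list durability at 8 months, leaves SAEs and infections blank.

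**Not collecting non-serious events, and having no data monitoring committee, are deliberate choices.** This stands. The protocol justifies both by the low risk of CE-marked clothing, and neither is criticised here.

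**Stronger readings that the protocol does not support.**

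- A reader might infer that the termination criterion cannot work. It can draw on SAEs and treated infections to month 6.
- A reader might take it for the only safety-based ground for stopping. The sponsor may discontinue for safety, the investigator may stop on major safety concerns, and the clinician evaluating SAEs may halt the trial.
- A reader might conclude that a garment reaction could never reach the steering committee. CTU staff are participants' main contact, and the management group reviews adherence and reports to that committee.
- A reader might claim that full follow-up would halve the zero-event upper bound from 3/150 = 2.0% to 3/300 = 1.0%. That treats controls' 2 months of wear as equal to the intervention arm's 6 to 8.

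**Conclusion.** The point holds for scheduled ascertainment. The protocol promises all SAEs during an 8-month participation, but its schedule for SAEs and for its one named safety endpoint ends at 6 months, when controls first receive the garments, and no later scheduled contact is stated to ask for either.

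Under 1:1 allocation, no dropout and continuous wear, up to about 40% of garment-exposed child-months are affected (33% at 2:1 silk to control, 50% at 1:2). Half or more of the late exposure at 1:1 is the controls', and all their first exposures fall there. The rest belongs to intervention children already followed for SAEs for 6 months.

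The primary outcome and the between-arm safety comparison to 6 months are untouched. The loss is confined to safety information from the open period. The mismatch between *severe* and *serious* is secondary: a point of wording to reconcile, not evidence that the trial lacks safety oversight.

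**What to change.** 1. State the SAE collection window under Adverse Events as randomisation to 8 months.
2. In Table 2, tick SAEs and treated skin infections at 8 months.
3. Add both items to the existing 8-month questionnaire, returned to the CTU so that research nurses remain blinded, and list them in the section that describes it.
4. Say that an SAE reported this way enters the procedure under Trial Intervention-related SAEs. That procedure now begins with the site, so one sentence is needed for events that reach the CTU first.
5. Reconcile Criteria for terminating trial with Safety endpoints and Adverse Events, so that the criterion refers to an event class that the trial collects. Which class that should be is for the trial team and the steering committee.

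Adding a reaction item to the weekly questionnaire would not close the gap, because the weekly questionnaires end at 6 months, before controls have worn the garments.

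The cost is a few questionnaire items and some CTU follow-up to verify parent-reported events, with no extra visit. The items would rely on parents' recall over two months, and the diary issued at 6 months could support that recall.

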### Trial Intervention-related SAEs

A serious adverse event that is unexpected in its severity and seriousness *and* deemed **directly related to or suspected to be related to the trial intervention** shall be reported to the ethics committee that gave a favourable opinion as stated below.

The event shall be reported immediately of knowledge of its occurrence to the Chief Investigator, and to the clinician named responsible for evaluating SAEs on the trial delegation log

The site will:

- Report all SAEs to the trial coordinating unit (Nottingham Clinical Trials Unit) via fax, using the University of Nottingham form (TA014).

The Trial Coordinating Unit will:

- Send SAEs to the CI and clinician delegated to evaluate SAEs.

The Clinician named responsible for evaluating SAEs will:

- Assess the event for seriousness, expectedness and relatedness to the trial treatment or intervention.
- Take appropriate medical action, which may include halting the trial and inform the Sponsor of such action.
- If the event is deemed related to the trial treatment or intervention shall inform the REC using the reporting form found on the NRES web page within 7 days of knowledge of the event.
- Shall, within a further eight days send any follow-up information and reports to the REC.
- Make any amendments as required to the study protocol and inform the REC as required

## **ETHICAL AND REGULATORY ASPECTS**

### **ETHICS COMMITTEE AND REGULATORY APPROVALS**

The trial will not be initiated before the protocol, informed consent forms and participant and GP information sheets have received approval / favourable opinion from the Research Ethics Committee (REC), and the respective National Health Service (NHS) Research & Development (R&D) department. Should a protocol amendment be made that requires REC approval, the changes in the protocol will not be instituted until the amendment and revised informed consent forms and participant and GP information sheets (if appropriate) have been reviewed and received approval / favourable opinion from the REC and R&D departments. A protocol amendment intended to eliminate an apparent immediate hazard to participants may be implemented immediately providing that the REC are notified as soon as possible and an approval is requested. Minor protocol amendments only for logistical or administrative changes may be implemented immediately; and the REC will be informed.

The trial will be conducted in accordance with the ethical principles that have their origin in the Declaration of Helsinki, 1996; the principles of Good Clinical Practice, and the Department of Health Research Governance Framework for Health and Social care, 2005.

Specific issues for the qualitative element are summarised below:

**Safety:** qualitative data will be collected using focus groups and individual interviews. Parent / guardians and children will participate in separate groups although they will be held concurrently in one large room in a local amenity. This will allow parent / guardians to maintain visual contact with their children at all times. Focus groups will be conducted at weekends or during school holidays to ensure that the children are not overtired. The Investigators who will conduct the child focus groups have considerable experience in interacting with young children and have enhanced CRB checks. They will be conversant with the current national guidance in relation to safeguarding children (Department of Education, 2013). If children do not wish to participate in the focus groups they will be able to return to their parent / guardian with ease.

## **INFORMED CONSENT AND PARTICIPANT INFORMATION**

The process for obtaining assent and parent / guardian informed consent will be in accordance with the REC guidance, and Good Clinical Practice (GCP) and any other regulatory requirements that might be introduced. The investigator or their nominee and the participant or other legally authorised representative shall both sign and date the Informed Consent Form before the person can participate in the study. Children who wish to do so, will also be able to provide "assent" to participation in the trial on the same form.

The participant (or parent/guardian) will receive a copy of the signed and dated forms and the original will be retained in the Trial Master File. A second copy will be filed in the participant's medical notes and a signed and dated note made in the notes that informed consent was obtained for the trial.

The decision regarding participation in the study is entirely voluntary. The investigator or their nominee shall emphasize to them that consent regarding study participation may be withdrawn at any time without penalty or affecting the quality or quantity of their future medical care, or loss of benefits to which the participant is otherwise entitled. No trial-specific interventions will be done before informed consent has been obtained.

The investigator will inform the participant (where appropriate) and their parent/guardian of any relevant information that becomes available during the course of the study, and will discuss with them, whether they wish to continue with the study. If applicable they will be asked to sign revised consent forms.

If the Informed Consent Form is amended during the study, the investigator shall follow all applicable regulatory requirements pertaining to approval of the amended Informed Consent Form by the REC and use of the amended form (including for ongoing participants).

